#### Criteria for discontinuing or modifying allocated interventions {11b}

Participants will be free to withdraw from the clinical study and choose other treatments (e.g. citicoline sodium tablets) if they feel their disease will not improve. Reasons for discontinuation of treatment may include but are not limited to, the following reasons: (1) participant becomes pregnant; (2) participant experiences serious side effects or complications; (3) participant takes other medicine during the study; (4) participant does not comply with the study protocol; and (5) participant requests withdrawal for other reasons.

#### Strategies to improve adherence to interventions {11c}

Frequent follow-up phone calls are an important aspect for monitoring adherence.

#### Relevant concomitant care permitted or prohibited during the trial {11d}

Participants will be informed and educated to refrain from all other therapies to improve visual function during the trial. IOP-control medications without the effect of optic nerve protection such as β-adrenergic blockers, adrenergic agonists, and carbonic anhydrase inhibitors are permitted.

### Provisions for post-trial care {30}

Not applicable.

#### Outcomes {12}

##### Primary outcomes

Primary outcomes help us to determine whether visual function is improved and whether BJYSP is effective. They will be as follows: (1) mean change in BCVA in the study eye will be measured at baseline and 2, 4, and 6 months thereafter; (2) mean change in values of the pattern standard deviation (PSD), mean defect (MD), square root of loss variance (sLV) in the study eye, as determined by an Octopus 900 perimeter, at baseline and 2, 4, and 6 months thereafter; (3) mean change in values of the latency of negative response 75 (LN75), amplitude of negative response 75 (AN75), latency of positive response 100 (LP100), and amplitude of positive response 100 (AP100) in the study eye, as determined by VTAS 2000 VEP, at baseline and 2, 4, and 6 months thereafter; and (4) mean change in values of the disk area (DA), cup area (CA), rim area (RA), cup volume (CV), rim volume (RV), cup/disk area ratio (C/DAR), linear cup/disk ratio (C/DLR), mean cup depth (mCD), maximum cup depth (maxCD), cup shape measure (CSM), height variation contour (HVC), mean RNFL thickness (MRNFLT), and RNFL cross-sectional area (RCSA) in the study eye, as determined by Heidelberg retina tomography II (HRT II), at baseline and 2, 4, and 6 months thereafter.

Potential participants will be told in detail of the purpose and content of research as well as the benefits and drawbacks of participating. Informed consent will be obtained by the designee at each site from those willing to participate. The schedule of visits and tests is shown in the SPIRIT Figure (Fig. 2). Participants will be reminded by telephone the week before the study visit by research nurses at each site.

**Fig. 2 Fig2:**
[figure not shown]
Measurement items and points of data capture. BJYSP Bujing Yishi tablet, HRT II Heidelberg Retina Tomography II, IOP intraocular pressure, TCM Traditional Chinese medicine, VEP visual evoked potential

##### Secondary outcomes

Secondary outcomes help us to know if the BJYSP improves TCM clinical symptoms and the changes in IOP: (1) mean change in IOP in the study eye, as determined by TOPCON CT 60 non-contact tonometer, at baseline and 2, 4, and 6 months thereafter; and (2) change in the number of patients with different grades of TCM symptoms, as determined by the investigators trained in SOPs according to TCM Symptom Score Scale (Table 1), at baseline and 2, 4, and 6 months thereafter.

##### Safety assessment

Safety assessments by three routine tests (blood, urine, and stool), electrocardiogram, liver function (alanine aminotransferase [ALT], aspartate aminotransferase [AST], alkaline phosphatase [ALP], gamma-glutamyl transferase [GGT], and serum total bilirubin [TBIL]) and kidney function (blood urea nitrogen [BUN], SCr, uric acid [UA], and β2-microglobulin) will be measured at baseline and 3 and 6 months thereafter.

### Participant timeline {13}

#### Sample size {14}

The calculation of the sample size is based on previous studies. The effective rate of mecobalamin tablets for GPCI was approximately 85% [17, 18], We hypothesized a 90% effective rate of BJYSP for GPCI in a larger sample size. According to the sample size of the estimation formula [19], α = 0.05, β = 0.10, in a two-sided test, P1 = 0.67, P2 = 0.871, two-sided u_α/2_ = u_0.05/2_ = 1.96, one-tailed u_β_ = u_0.1_ = 1.282. We put these values into the formula n^1^ = n^2^= $$ \frac{1}{2}{\left[\frac{{\mathrm{u}}_{\upalpha /2}+{\mathrm{u}}_{\upbeta}\ }{\sin^{-1}\sqrt{p_1}-{\sin}^{-1}\sqrt{p_2}}\right]}^2 $$, resulting in n^1^ = n^2^= $$ \frac{1}{2}{\left[\frac{1.96+1.282\ }{\sin^{-1}\sqrt{0.67}-{\sin}^{-1}\sqrt{0.871}}\right]}^2=87.86. $$ That is, approximately 88 cases in the BJYSP group and in the control group or 176 cases in both groups. To account for a 20% dropout rate, the calculation 176 + (176 × 20%) = 211.2 suggests that 212 patients should be recruited. We rounded this value to 216 patients in total.

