### Statistical methods

#### Statistical methods for primary and secondary outcomes {20a}

Statisticians will independently undertake statistical analysis. All data will be presented as the means ± standard deviation (SD). Statistical analysis will be performed by SPSS 21.0 software (SPSS Inc., Chicago, IL, USA). All statistical tests will be two-sided tests, and the statistical significance threshold will be set at *P* < 0.05. The chi-square test will be used for categorical variables, an independent Student’s t-test will be used on measurement data, and rank-sum test will be used for grade data. To assess covariate balance, baseline characteristics will be summarized and compared between the BJYSP group and the control group by means of simple descriptive statistics.

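### The sample size is justified on a binary effective rate that is not among the listed outcomes, so the stated 90% power applies to none of the 21 primary comparisons of mean change

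*Protocol article*

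**What the plan says.** **Sample size {14}.** The section opens with "The effective rate of mecobalamin tablets for GPCI was approximately 85" per cent and continues "We hypothesized a 90% effective rate of BJYSP for GPCI in a larger sample size". The error rates are "α = 0.05, β = 0.10, in a two-sided test". The values put into the arcsine formula for two proportions are "P1 = 0.67, P2 = 0.871". The result is "approximately 88 cases in the BJYSP group and in the control group or 176 cases in both groups", raised to 212 for dropout and then rounded to 216.

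**Primary outcomes (Outcomes {12}).** There are four groups, all expressed as mean change. The first reads "mean change in BCVA in the study eye will be measured at baseline and 2, 4, and 6 months thereafter". The others are three perimetry indices, four VEP latencies and amplitudes, and thirteen HRT II parameters.

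**Secondary outcomes.** These are mean change in IOP and the change in numbers of patients in different TCM symptom grades.

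**Statistical methods {20a}.** A chi-square test is given for categorical variables in general. For the rest, an independent Student's "t-test will be used on measurement data, and rank-sum test will be used for grade data".

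**The concern.** A power statement belongs to one variable, one contrast and one test. Here the variable in the calculation (a yes/no classification of effectiveness) and the variables to be tested (continuous changes) are different. The article gives no measure, threshold or time point that would turn any of the 21 changes into effective or not effective. It also gives no target difference or SD for any of them.

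The practical result is that nobody can say what difference the trial was built to detect on any primary variable, so a null result would be hard to interpret. A further risk is that an effective rate could be constructed late, in an open-label trial, and presented as the outcome for which the trial was powered. The article does not show that this is intended. It only does not rule it out.

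**Working it through.** **1. Reproduce the plan's figure.** Inputs from Sample size {14}: u(α/2) = 1.96, u(β) = 1.282, P1 = 0.67, P2 = 0.871.

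- arcsin√0.67 = 0.9589; arcsin√0.871 = 1.2034; difference = 0.2446
- n per group = ½ × (3.242 / 0.2446)² = 87.86, taken as 88
- 88 × 2 = 176; 176 × 1.2 = 211.2, taken as 212, then 216 (108 per arm at 1:1)

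The arithmetic is right for the rates entered. A pooled-variance formula gives a similar 90 per group.

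**2. Look for the outcome that this calculation powers.**

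| Where | What is listed | Type |
|---|---|---|
| Primary (1) | BCVA change: 1 variable | continuous |
| Primary (2) | PSD, MD, sLV change: 3 | continuous |
| Primary (3) | VEP latencies and amplitudes, change: 4 | continuous |
| Primary (4) | HRT II parameters, change: 13 | continuous |
| Secondary (1) | IOP change | continuous |
| Secondary (2) | TCM symptom grades | ordinal |
| Sample size {14} | effective rate | binary, undefined |

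1 + 3 + 4 + 13 = 21 primary variables, none binary. The last row matches no other row. Changing the pair of rates does not help, because any pair of rates still sizes a comparison that is not listed.

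**3. What the fixed n delivers for one continuous variable.** The article gives no SD, so the differences below are in SD units and are assumptions, shown as a range. Normal approximation, two-sided alpha 0.05.

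Detectable difference d = (z for alpha + z for power) × √(2/n):

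- 88 per arm, 90% power: 3.242 × √(2/88) = 3.242 × 0.1508 = 0.49 SD
- 88 per arm, 80% power: 2.802 × 0.1508 = 0.42 SD
- 108 per arm, 90% power: 3.242 × √(2/108) = 3.242 × 0.1361 = 0.44 SD

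The 88 corresponds to a per-protocol set after the planned losses. The 108 corresponds to a full analysis set in which the last value is carried forward, so that nobody is lost from the comparison. The section on missing data {20c} requires both sets.

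Power = Φ(d × √(n/2) − 1.96):

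| True difference | 88 per arm | 108 per arm | n per arm for 90% power |
|---|---|---|---|
| 0.2 SD | 26% | 31% | 526 |
| 0.3 SD | 51% | 60% | 234 |
| 0.4 SD | 76% | 84% | 132 |
| 0.5 SD | 91% | 96% | 85 |

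With 88 per arm, actual power on a primary variable could thus lie anywhere from about a quarter to above 90%, depending on a difference that the article does not state.

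**The case against.** The document is a condensed article. A full protocol or analysis plan could define a responder, and the two studies cited for the 85% may do so. The text also holds two traces of such an analysis: the general chi-square line, and the rule in {20c} that a participant with missing data enters the full analysis set in an invalid way, which may mean counted as not effective. This stands to the extent that one cannot say the effective rate will never be analysed, only that this article neither lists nor defines it. It does not remove the mismatch. The article does state its primary outcomes and its basis for sample size, and a further document could reconcile them only by contradicting one of the two.

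A reader might infer that the trial is underpowered. The article does not support that: 88 per arm would serve well for a true difference near 0.5 SD, and nothing here shows that the difference is smaller.

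A reader might also want to add the loss of power from testing 21 variables. That is a question of multiplicity. The plan splits no alpha, and the loss would arise under a correctly matched calculation too.

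**Conclusion.** The point holds in a limited form. The stated 90% power applies to none of the 21 listed primary comparisons, and the mismatch lies within the article itself. Its size cannot be given as a corrected n, because no target difference or SD is stated. What can be said is that 216 recruited patients give 90% power for about 0.44 SD (108 per arm) to 0.49 SD (88 per arm) on a single continuous variable. These figures assume 1:1 allocation, one test at two-sided 0.05, the normal approximation, and no loss of precision from carrying values forward. Whether such a difference is plausible or worthwhile cannot be judged from the article.

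**What to change.** Before database lock, with n kept at 216, take one of two routes.

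**(a) Match the calculation to a continuous outcome.** Name one primary variable and one time point. Replace the effective-rate calculation with what the trial delivers for that variable: 90% power for about 0.49 SD with 88 evaluable per arm (per-protocol set) or about 0.44 SD with all 108 (full analysis set), and about 51% at 0.3 SD and 76% at 0.4 SD with 88. Add an SD with its source, so that the difference can be read in clinical units. The article cites its earlier studies only for an effective rate, so whether they supply that SD has to be checked.

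**(b) Match the outcome to the calculation.** Define the effective rate (variable, threshold, time point, chi-square test) and make it the primary outcome. This route must also settle which rates are meant. The text gives 85% and 90% but the formula uses 0.67 and 0.871. For 85% against 90% the same formula needs about 911 per group, and 88 per group has about 17% power.

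**Cost.** Neither route adds patients. Under (a), the justification becomes a detectable effect size, which may look less favourable than a flat 90%, and one primary variable must be chosen. Under (b), the primary outcome list must be amended. Either change goes to the ethics committee, as the article's own amendment section provides for changes to outcomes and analyses.

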### Assignment of interventions: allocation

#### Sequence generation {16a}

After obtaining the written informed consent from the participants and baseline screening, all eligible patients will be stratified according to early, moderate, and advanced stages of glaucoma [20]: early glaucoma patients have an early glaucomatous visual field loss defined as an MD ≥ − 6 dB; moderate glaucoma patients have a moderate glaucomatous visual field loss defined as MD ≤ − 6 to ≥ − 12 dB; and advanced glaucoma patients had an advanced glaucomatous visual field loss defined as MD ≤ − 12 to ≥ − 20 dB. Random numbers of 001–216 will be automatically generated by SAS software (whole random numbers). Among them, the random numbers 001–072 are assigned to the early stage, the random numbers 073–144 are assigned to the moderate stage, and the random numbers 145–216 are assigned to the advanced stage. After stratifying, the participants will be randomly assigned to the BJYSP group or control group with a ratio of 1:1. An overview of case distribution of each center, specific measurements, and time points of data collection can be found in the SPIRIT Figure (Fig. 2).

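### The sample size paragraph hypothesises 85% versus 90% but calculates with 67% versus 87.1%; for the hypothesised difference the trial has about 17% power, not 90%

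*Protocol article*

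**What the plan says.** Everything is in one paragraph of the protocol article, Sample size {14}.

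- Control rate, attributed to previous studies: "The effective rate of mecobalamin tablets for GPCI was approximately 85" per cent.
- Rate expected on the test drug: "We hypothesized a 90% effective rate of BJYSP for GPCI in a larger sample size".
- Error rates: "α = 0.05, β = 0.10, in a two-sided test".
- Values put into the arcsine formula: "P1 = 0.67, P2 = 0.871". The same two values appear again in the worked formula, which gives 87.86.
- Result: "approximately 88 cases in the BJYSP group and in the control group or 176 cases in both groups".
- Dropout: 20% of 176 is added to 176, giving 211.2, which "suggests that 212 patients should be recruited". This is then rounded up to 216.

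Sequence generation {16a} fixes equal allocation, so 216 means 108 per group.

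**The concern.** Neither rate given in words enters the formula, and neither rate in the formula is introduced in words. The hypothesised difference is 5 points and the one used is 20.1 points. If P1 is the control rate, it lies 18 points below the control rate the paragraph has just cited. P2 (0.871) is close to that cited control rate of 0.85. The paragraph does not say which group P1 and P2 belong to and attaches no reference to them.

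The total of 216 and the 90% power are the main planning figures, and 216 also fixes the randomisation lists (72 numbers per disease stage). If the hypothesis in words is the real one, the trial would very probably miss a true difference of that size. A non-significant result would then be read as evidence against benefit from a trial with 90% power. As printed, a reader cannot tell what effect the trial was sized to detect.

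The dropout step raises a second, smaller question: adding 20% to the required number does not leave that number after 20% are lost.

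**Working it through.** **Inputs, all from Sample size {14} and Sequence generation {16a}:** two-sided alpha 0.05 (u = 1.96); beta 0.10 (u = 1.282); equal allocation; rates in words 0.85 and 0.90; rates in the formula 0.67 and 0.871; 88 per group required; 20% dropout; 216 recruited.

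**Formula (the protocol's own, angles in radians):** n per group = ½ × [(1.96 + 1.282) / d]², where d = |asin√p₁ − asin√p₂|.

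**1. Reproduce the printed figure.** asin√0.67 = 0.9589 and asin√0.871 = 1.2034, so d = 0.2446. Then n = ½ × (3.242/0.2446)² = 87.86. This matches the document, so the calculation is right for those inputs.

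**2. Use the rates in words.** asin√0.85 = 1.1731 and asin√0.90 = 1.2490, so d = 0.07595. Then n = ½ × (3.242/0.07595)² ≈ 911 per group, about ten times 88 (911/88 = 10.4). A pooled two-proportion formula gives 918.

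**3. Power for each pair at the planned size.** Inverting the formula, power ≈ Φ(√(2n) × d − 1.96). The chance of a significant result in the wrong direction adds only about 0.1 to 0.2 points for 85% vs 90%.

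| Evaluable per group | 85% vs 90% | 67% vs 87.1% |
|---|---|---|
| 86 (216 less 20%) | 17% | 89.4% |
| 88 (planned) | 17% | 90.1% |
| 108 (no loss) | 20% | 94.9% |

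At 88 per group and 85% vs 90%: √176 × 0.07595 = 1.008, and Φ(1.008 − 1.96) = 0.170, or 0.172 with both tails. The pooled normal approximation gives 16.9%, and exact enumeration of the uncorrected chi-square test gives 16.8%. A one-sided 0.05 test, which the protocol does not plan, would give only 26%.

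**4. What 88 per group can detect from an 85% control rate.** The required d is 3.242/√176 = 0.2444. Adding 1.1731 gives 1.4175, and sin²(1.4175) = 0.977. BJYSP would have to reach about 97.7%.

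**5. Dropout.** 176 × 1.20 = 211.2, but 211.2 × 0.80 = 168.96, so 176 are not retained. 176/0.80 = 220 retains them. The 216 chosen leave 216 × 0.80 = 172.8, about 86 per group, with 89.4% power at 0.67/0.871.

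**The case against.** The strongest reply is that 0.67 and 0.871 may be the real planning rates and the 85%/90% sentences the mistake. The 90% power would then stand. The document does not show which pair was intended, so this cannot be excluded, and the 17% applies only to the difference stated in words. That does not save the paragraph: on this reading, its cited control rate and its stated hypothesis are both wrong.

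The references cited for the 85% cannot be seen and might also contain 0.67 or 0.871. It is therefore fair to say that no source is attached to those values, not that none exists.

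A non-inferiority design could make a small expected difference workable. However, the article gives no margin, and Statistical methods {20a} makes all tests two-sided at 0.05.

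Two further points stand as limits on this finding. First, the effective rate is not among the outcomes listed under Outcomes {12}; the primary ones are mean changes. Both 90% and 17% therefore describe power for a rate the article does not list, and correcting the rates does not by itself tie the sample size to those outcomes. Second, the dropout slip is small. The section on missing data {20c} carries the last value forward and keeps such cases in the Full Analysis Set, so that set could be as large as 108 per group. Even then, power for 85% versus 90% is only about 20%.

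**Conclusion.** The concern holds. The paragraph contains two incompatible pairs of rates. With two-sided alpha 0.05 and the protocol's own formula, 88 per group give 90% power for 67% versus 87.1% and about 17% for 85% versus 90%, the difference the protocol says it hypothesises. The latter would need about 911 evaluable patients per group. The conclusion does not depend on the method (arcsine, pooled normal or exact chi-square) or on dropout: across 86 to 108 evaluable per group, power for the stated hypothesis stays between about 17% and 20%.

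The dropout step is also wrong, but its effect is minor: 172.8 evaluable instead of 176, and 89.4% instead of 90.1% power under the rates used. The main contradiction must be corrected because it leaves the justification for the trial's size undefined.

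**What to change.** Rewrite the Sample size section around one pair of rates, naming the group each belongs to, in one of two ways:

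- If 0.67 and 0.871 are the planning rates, cite their source and delete the 85% and 90% sentences.
- If 85% and 90% are the planning rates, state that 88 per group give about 17% power for that difference, and that 90% power is reached only for about 85% versus 98%.

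In either case, replace the dropout step with 176/(1 − 0.20) = 220, or keep 216 and state that it leaves about 172 evaluable patients. Under 0.67/0.871 that gives about 89% power.

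The cost is rewording one paragraph and, under the second option, reporting a much less favourable power. No additional patients and no change to the conduct of the trial are requested, so the stage of recruitment is no obstacle.

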#### Methods in analysis to handle protocol non-adherence and any statistical methods to handle missing data {20c}

Due to the anticipated small number of missing data, we will dispose missing data by transfer the last data to the final data. The data of this participant will be entered into the Full Analysis Set (FAS) in an invalid way, and this case will not be entered into the Per Protocol Set (PPS). Finally, the statistical significance of FAS and PPS will be analyzed. If the statistical significance was consistent, there was statistical difference.

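### The 20% dropout allowance is added to the 176 required cases instead of dividing them by 0.80, so the planned 216 leaves 172.8, slightly short of 176

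*Protocol article*

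**What the plan says.** Protocol article, Sample size {14}. The inputs to the formula are "α = 0.05, β = 0.10, in a two-sided test, P1 = 0.67, P2 = 0.871". The arcsine formula is printed with its result, 87.86, from which the section takes "approximately 88 cases in the BJYSP group and in the control group or 176 cases in both groups". The next step allows for a dropout rate of 20%: "the calculation 176 + (176 × 20%) = 211.2 suggests that 212 patients should be recruited", followed by "We rounded this value to 216 patients in total".

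Sequence generation {16a} uses the 216 as three severity strata of 72, randomised 1:1.

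The section on non-adherence and missing data {20c} carries the last value forward for a participant with missing data and keeps that participant in the Full Analysis Set (FAS). It also states that "this case will not be entered into the Per Protocol Set (PPS"). Significance is then examined in both sets and compared.

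**The concern.** The article calls the 20% a dropout rate, and nowhere gives it another meaning. Such a rate applies to the patients who enter the trial, not to those who are left at the end. Adding 20% of the final number to itself therefore gives too small a recruitment target, and the target does not reach the purpose the section sets for it.

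At stake is whether the stated power (β = 0.10) survives the dropout that the plan itself expects. The shortfall falls on patients without dropout, who are the ones that can enter the Per Protocol Set (PPS). Because {20c} looks for agreement between FAS and PPS, the size of the PPS has some bearing on the conclusion.

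**Working it through.** **Inputs, all from Sample size {14}:** two-sided α = 0.05 (u = 1.96), β = 0.10 (u = 1.282), P1 = 0.67, P2 = 0.871, dropout 20%, final total 216.

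**1. The article's base figure.** The distance between the two rates on the arcsine scale is

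Δ = |sin⁻¹√0.67 − sin⁻¹√0.871| = 0.24457

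n per group = ½ × [(1.96 + 1.282)/0.24457]² = 87.86, rounded up to 88, or 176 in total. This reproduces the printed figure.

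**2. The article's allowance.** 176 × 1.20 = 211.2, rounded up to 212. This also reproduces.

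**3. The allowance for a rate that applies to those recruited.** N × (1 − 0.20) = 176, so N = 176/0.80 = 220.

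**4. What each total leaves, and the power it gives.** Power = Φ(Δ√(2n) − 1.96), with n the number remaining per group.

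| Recruited | Left after 20% dropout | Short of 176 | Largest dropout that still leaves 176 | Left per group | Power, 0.67 vs 0.871 |
|---|---|---|---|---|---|
| 212 | 212 × 0.80 = 169.6 | 6.4 | 1 − 176/212 = 17.0% | 84.8 | 89.0% |
| 216 | 216 × 0.80 = 172.8 | 3.2 | 1 − 176/216 = 18.5% | 86.4 | 89.5% |
| 220 | 220 × 0.80 = 176 | 0 | 20.0% | 88 | 90.05% |

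For 216, for example: 0.24457 × √172.8 − 1.96 = 1.255, and Φ(1.255) = 0.895.

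**5. Effect of the rounding.** The allowance is 220 − 212 = 8 patients too small. Moving to 216 recovers 4 of them. The article describes that move only as rounding.

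**6. Independence from the base figure.** Since 1.20 × 0.80 = 0.96, this method leaves 4% fewer patients than required before rounding, whatever number it starts from.

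**The case against.** The case for leaving this alone has four parts.

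- **It is immaterial.** The number that counts is 216, not 212, and it lies 4 patients (1.8%) below 220. The choice of formula matters as much: the pooled two-proportion formula gives 90 per group (180 in total, also 4 more than 176), and with continuity correction it gives 100 per group. This stands, and it is why the point is minor.
- **The article does not say that 176 must be completers.** It speaks only of cases. Dropouts stay in the FAS with their last value, so by head count the FAS is not short. That is true of the FAS. But the section enlarges 176 expressly because of dropout, so it means 176 to be left after losses. Carry-forward does not cancel an allowance that the plan itself makes.
- **The rule comparing FAS and PPS is unclear.** The sentence in {20c} does not plainly require significance in both sets, nor does it say that the PPS is to be powered. This stands in part. The arithmetic does not depend on it, and what is clear is that these cases leave the PPS and that the two sets are compared.
- **The base figure is itself unsupported.** The text gives effective rates of about 85% and 90%, while the formula uses 0.67 and 0.871. With 85% against 90% the same formula needs about 912 per group, and power at 88 per group would be about 17%. This stands and is far more serious. It is a separate defect: it makes the power figures above conditional, but it does not make the dropout step right.

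**Conclusion.** The concern holds and is minor. The dropout step is wrong as written: 20% dropout calls for 220 recruited, not 212, and rounding to 216 closes half of that gap. At 20% dropout the trial would keep 172.8 patients against the 176 required. Power would be about 89.5%, roughly half a percentage point below the 90.05% that 88 per group gives. The planned 216 meets the requirement up to 18.5% dropout.

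Two assumptions underlie this. The 20% is a share of those recruited, which is the ordinary meaning of a dropout rate and the only one the article supports. The power figures take 0.67 against 0.871 and the printed arcsine formula as given; they say nothing about power under 85% against 90%.

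**What to change.** In Sample size {14}, replace the allowance by 176/(1 − 0.20) = 220. Keep 216 and say so openly: it leaves 172.8 patients at 20% dropout, with about 89.5% power if the rates are 0.67 and 0.871, and it retains the full 176 for dropout up to 18.5%. The power figure should carry that condition in the same sentence, so that it does not lend support to rates that the text contradicts.

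The cost is one corrected line and a slightly less favourable figure. The three strata of 72 in {16a} stay as they are. A total of 220 would not divide into three equal strata at 1:1; the next total that does is 222 (74 per stratum, 37 per group within each). With recruitment under way since June 2018 according to Trial status, a gap of 4 patients does not justify changing the randomisation list.

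If the base number is recalculated once the rates are reconciled, divide the new number by 0.80 so that the same error is not carried over.
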